## Abstract

**Background::**

Panic disorder (PD), defined by repeated and unexpected panic attacks, severely affects patients’ living quality and social function. Perimenopausal women are high-risk group of PD and suffer greatly from it. Modern medicine therapies for this disorder have many side reactions and poor effects, so nonpharmacological modality is an urgent need. Although acupoint catgut embedding is widely used in clinical practice, there is no persuasive evidence of its effect for perimenopausal PD. The aim of this study is to investigate the effectiveness and safety of acupoint catgut embedding for perimenopausal PD and to elucidate the correlations among brain neural activation, bio-markers (amino acids) and clinical outcomes with radiographic evidence, thus to explore its neural mechanism.

**Methods::**

The parallel designed, exploratory randomized controlled trial will include 70 outpatients with perimenopausal PD recruited from two hospitals of Chinese Medicine. These subjects will be randomly allocated to an intervention group (Group Embedding) and a control group (Group Medication) in a 1:1 ratio. The subjects in the intervention group will receive acupoint catgut embedding treatment two weeks a time in the following predefined acupuncture points: Shenshu (BL23), Sanyinjiao (SP6), Guanyuan (RN4), Ganshu (BL18), Zusanli (ST36) and Pishu (BL20). The included women of the control group will take 0.4 mg Alprazolam tablet orally, 1 tablet a time, 3 times a day. There is a study period of 3 months and a follow-up period of 1 month for each group. The primary outcomes will be the following therapeutic indexes: the frequency of panic attack, Panic Disorder Severity Score (PDSS), and Panic-associated Symptoms Score (PASS) during the observation period and follow-up period. The changes in Hamilton Anxiety Scale (HAMA) Score and Symptom Checklist 90 (SCL-90) Score will also be compared between these two groups. Additionally, functional magnetic resonance imaging (fMRI) and proton magnetic resonance spectroscopy (1H-MRS) scans will be done before and after the observation period to show cranial neuroimaging changes.

**Discussion::**

We present a study design and rationale to explore the effectiveness and neural mechanism of acupoint catgut embedding for perimenopausal PD. There are still several factors restrict our research such as no unified standard of diagnostic criteria and curative effect evaluation.

**Trial registration::**

Chinese Clinical Trial Registry, ChiCTR-INR-16009724, registered in November 2016.

## Introduction

1

The definition of panic disorder (PD) is repeated and unexpected panic attacks.^[1]^ It is common in the general population with a lifetime prevalence of 1.6% to 2.2% and has a high recurrence rate.^[2]^ The main features of PD are excessive and persistent fear and related behavioral disturbances. Attacks are usually accompanied by tachypnea, dizziness, palpitation, tremor, and sweating. Because of PD's sudden onset and a strong sense of impending death, this disease severely affects patients’ living quality and social function, bringing a heavy financial burden on families and society.^[3]^ Perimenopausal women are the high-risk group of PD. They are at a special time when disease intervention is particularly important.

Modern medicine therapies towards perimenopausal PD, such as hormone replacement therapy, rnon-hormonal medication therapy, and cognitive behavioral therapy have many flaws, like the variety of side effects, high recurrence rate, drug dependence, and so on.^[4]^ Clinical medications such as Selective Serotonin Reuptake Inhibitors (SSRI), serotonin-norepinephrine reuptake inhibitors (SNRI), tricyclic antidepressants (TCA), and benzodiazepines (BDZ) are efficacious in the treatment of PD. However, approximately 20% to 40% of PD patients do not fully respond to pharmacotherapy.^[5,6]^ As the “gold standard” of psychotherapy for it, cognitive behavioral therapy (CBT) still does not increase the cure rate.^[7]^ Recently, therapy combining drugs and CBT has become a noticeable research field of PD treatment. It shows great clinical effects in short terms, but still fails to fill this gap. Moreover, 25% to 50% of patients relapse within 6 months after drug discontinuation. Up to 50% of patients suffer from residual panic phobic symptoms after treatment. And more than 30% of patients are still afflicted with a full-blown disorder after 3 to 6 years.^[8]^ From a clinical point of view, a strong need for effective, fast acting and tolerable therapeutic treatments for PD still exists.^[5]^ Therefore, investigating the pathogenesis and seeking for valid curative measures are quite essential to perimenopausal patients, for both their body and mind health care.

Studies have reported that in patients with an anxiety disorder, increased excitatory neurotransmission by glutamate or decreased inhibitory signaling by Gamma-aminobutyric acid (GABA) could be the reasons of increased activity in the emotion-processing brain regions.^[9]^ The drop of inhibitory GABA, leading to an imbalance of Glutamate-GABA, is known as the basic cause of PD.^[10,11]^ Perimenopausal symptoms are related to disruptions to nervous and endocrine systems. The metabolic disorder of amino acid could cause the excitatory and inhibitory imbalance of brain function.^[12]^ In previous research, ovariectomized (OVX) rats were used as models of female climacteric state. OVX caused the elevations of both essential and non-essential amino acids in blood plasma, creating outstanding disruptions in amino acid metabolism. But whether or not that perimenopausal PD patient's neural activity status and neural conductive mechanism are related to the drop of inhibitory GABA still remains unclear. In addition, acupoint catgut embedding restored all the OVX-induced changes except for total cholesterol in plasma. Therefore, this therapy has been proved to modulate amino acid closely related to emotion regulation of OVX rats.^[13]^

Nowadays, acupoint catgut embedding is widely applied in the clinical practice of perimenopausal syndrome, but there is no persuasive evidence of its effect on perimenopausal panic disorder. Hence, some sensible evidence of its effectiveness and safety in treatment of perimenopausal PD is urgently needed. Imaging techniques can provide an effective approach to study the functional brain region. With the help of fMRI and 1H-MRS, the changes in neural activity before and after the study can be gathered. Thus, pathogenesis of perimenopausal PD may be revealed as well as the neural mechanism of acupoint catgut embedding treatment.

## Methods/design

2

### Trial design

2.1

This is a parallel designed, exploratory randomized controlled trial with a 1:1 allocation to the intervention group (Group Embedding, n = 35) and the control group (Group Medication, n = 35). The study is intended to investigate the effectiveness and safety of acupoint catgut embedding for perimenopausal PD. The other objective is to explore the central nervous mechanism of this disease, to research the internal relationship between neural activity and amino acid metabolism with the use of fMRI and 1H-MRS. The protocol adheres to the SPIRIT 2013 statement. The trial will be done in the the Bao’an District TCM Hospital, the Affiliated Hospital of Guangzhou University of Chinese Medicine.

### Study subject

2.2

All the subjects are menopausal syndrome specialist clinic patients from the perimenopausal syndrome clinical research base of Guangdong Provincial Hospital of Traditional Chinese Medicine and the Bao’an District TCM Hospital, the Affiliated Hospital of Guangzhou University of Chinese Medicine.

### Recruitment

2.3

There are 3 ways to recruit participants: ① Recruit from clinic patients of cooperative hospitals. We will gather each hospital's director of acupuncture department and gynecology department and call a seminar focusing on how to recruit participants. Then we will send assistants to each department to assist screen participants. Clinical trial information will be posted on the bulletin boards of these hospitals. ② Recruit via broadcasting, TV and newspapers, etc. ③ Attract suitable participants by introducing some basic knowledge about perimenopausal physiology, perimenopausal pathology and its treatment in community service.

### Eligibility criteria: inclusion criteria

2.4

1.Corresponding to diagnosis standards of PD;2.Female, aged 41 to 60, at least junior middle school literacy;3.HAMA score ≥ 14;4.Patients who consent to sign informed consent form.

### Eligibility criteria: exclusion criteria

2.5

1.Combined with other mental disorders, such as phobia and melancholia, or PD caused by somatoform disorders;2.Combined with severe cardiac and hepatic and renal insufficiency, or other serious diseases of other systems like malignant tumors;3.PD caused by physical diseases like epilepsy, heart attack, pheochromocytoma, hyperthyroidism, or spontaneous hypoglycemia, etc;4.Patients who used antipsychotic drugs, antidepressive drugs, or sex hormones within 2 weeks before included, or combined taking other therapies like cognitive behavioral therapy etc;5.Patients who have contraindications to MR, like having aneurismal clips, implantable neuro-stimulator, pacemaker, implantable automatic defibrillator, cochlear implantation or visual obstacles;6.Female during pregnancy or lactation;7.Patients who suffered from alcohol or drug abuse within 1 year or with a history of alcohol or drug dependency.

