#### Control group

2.9.2

In the 3-months study period, patients in the control group will take Alprazolam tablet (Guangxi Southpearl Pharmaceutical Co., Ltd.) with the size of 0.4 mg orally, 1 tablet a time, 3 times a day.

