### Adverse events

2.12

In research, some adverse reactions may occur.

1.There are a few common responses after the acupoint catgut embedding:Local reactions: Mostly some sterile inflammations with inflamed hot pain occur within 5 days. Some cases may be more severe, like a small amount of milky-white exudation at the embedding spot caused by fat liquefaction because of suture stimulation. Circumstances above should not require any special treatment.General reactions: Some patients may experience temperature rising after treatment 4 to 24 hours, mostly around 38. It will fade away in 2 to 4 days by itself. Usually, hemogram of each patient may rise in different levels, and it will return to normal in 3 to 5 days.2.There are a few adverse responses after the acupoint catgut embedding:Pain: Apply hot compress if there is pain at embedding acupoint.Secondary infections: Lack of strict asepsis and inappropriate protection for the wound could cause secondary infection, which mostly brings about some inflammatory symptoms like local swelling, progressive pain, and fever in 3 to 4 days after the implantation. Hot compress and anti-infective treatment would be helpful.Nerve injuries: It is usually caused by an incorrect operation or excessive stimulation or carelessness, and can be avoided with careful operation.Hemorrhage: It is usually caused by a puncture on the vessels or excessive stimulation. Pressure put on the puncture point would stop the bleeding.Suture allergies: Local itching or swelling or fever can be remitted by antianaphylaxis treatment.3.Alprazolam is one of the Benzodiazepines. Its principal effects are anti-anxiety and antidepressant. Common adverse reactions are as following:Somnolence, vertigo, and weakness, etc. The large dose may cause dystaxia, tremor, uroschesis or jaundice.Addiction. Drug withdrawal may cause withdrawal symptoms after being used for a long period, showing as emotional or melancholy.A few patients may suffer dry mouth, inattention, hyperhidrosis, palpitation, constipation or diarrhea, blurred vision, and hypotension.

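### Exclusion 4 sets a 2-week washout for three drug classes but omits benzodiazepines, the comparator's own class, so a woman who has just stopped one can enter

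*Protocol article*

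**What the plan says.** Exclusion item 4 in section 2.5 of the protocol article has two parts. The drug part excludes women who "used antipsychotic drugs, antidepressive drugs, or sex hormones within 2 weeks before included". It names three classes and one window and has no open-ended wording. The second part excludes women "combined taking other therapies like cognitive behavioral therapy etc", with no window before inclusion. Item 7 excludes "alcohol or drug abuse within 1 year or with a history of alcohol or drug dependency".

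The Introduction (section 1) lists benzodiazepines as a class of their own beside SSRIs, SNRIs and tricyclics, and says that "benzodiazepines (BDZ) are efficacious in the treatment of PD". Section 2.12 states that "Alprazolam is one of the Benzodiazepines" and that "Drug withdrawal may cause withdrawal symptoms after being used for a long period". Under section 2.9.2 the control group takes alprazolam "with the size of 0.4 mg orally, 1 tablet a time, 3 times a day" for the three-month study period.

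Section 2.9 places the baseline scores before randomization and repeats them every 4 weeks. Section 2.10.1 defines the primary outcomes as changes in attack frequency, PDSS and PASS.

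**The concern.** The washout exists so that earlier psychoactive or hormonal treatment does not affect the baseline or the first weeks on study. The protocol applies it to antidepressants but not to the class used as comparator, which by its own account is an effective treatment for the condition. Prior use in women who present with panic disorder is therefore foreseeable.

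A woman who stopped a benzodiazepine just before inclusion may have her baseline measured under residual drug benefit, or during withdrawal. If she is allocated to medication, she restarts the class. If she is allocated to embedding, she stays off it, and the loss of benefit or the course of withdrawal is then seen in her scores. Because the primary outcomes are changes in these scores, this can affect them differently in the two arms. The entry threshold of HAMA ≥ 14 (section 2.4) may be affected in the same way.

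**Working it through.** **Does any clause cover recent, ordinary benzodiazepine use?**

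| Clause | What it reaches | Covers a woman who has just stopped? |
|---|---|---|
| 2.4, inclusion criteria | Diagnosis, age, literacy, HAMA, consent | No |
| 2.5 item 4, drug list | Antipsychotics, antidepressants, sex hormones; 2 weeks | No, class not listed |
| 2.5 item 4, other therapies | At most, current use | No, no look-back |
| 2.5 item 7 | Abuse within 1 year, or any history of dependency | Not ordinary prescribed use |
| 2.6 item 4 | Unpermitted medicines during the trial | No, applies after entry |

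One reading narrows the gap. Section 2.12 says of alprazolam that "Its principal effects are anti-anxiety and antidepressant", so a screener might count alprazolam itself as an antidepressant. That is said of alprazolam only, and the Introduction keeps benzodiazepines apart from the antidepressant classes. Other benzodiazepines are still not reached.

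**What can be quantified.** The protocol gives no figure on this point to reproduce. What follows from its other figures:

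- Weight of one woman: 35 per arm (section 2.1), so 1/35 = 2.9% of her arm. With the 20% loss allowed in section 2.13, 70 × 0.8 / 2 = 28 per arm, so 1/28 = 3.6%.
- Difference in treatment from week 0: 3 × 0.4 mg = 1.2 mg alprazolam a day in the medication arm, none in the embedding arm.
- Timing: week 0 to week 4 is 28 days. If inclusion and week 0 coincide, a woman in the embedding arm who stopped the day before spends that whole interval in her first month off the drug. A 2-week window would put 14 of those 28 days, one half, before baseline.
- Reach: counting follow-up as one assessment, there are 4 after baseline (weeks 4, 8, 12 and follow-up). Only the first closes that interval, so 1 of 4 is mainly affected.

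**Direction.** Residual benefit at baseline makes the starting score too low, so its loss looks like worsening in the embedding arm. Withdrawal at baseline makes the starting score too high, so its resolution looks like improvement there. The two work against each other, and no net direction can be derived.

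**The case against.** The strongest reply is that this is not confounding. Recent users are allocated by chance, and what differs afterwards is the assigned treatment. A former user who does better on restarting alprazolam, or worse without it, shows the effect of allocation in that kind of patient. This stands in part: the randomized comparison remains valid for the women enrolled, and a former user who stays off the drug in the embedding arm otherwise gives the planned contrast. But the contrast in such women also contains the end of an earlier treatment, which the protocol's own washout is meant to keep out.

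Other points against:

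- **The group may be small.** Item 7 removes women with a history of dependency, and section 2.12 ties withdrawal symptoms to long use, so the withdrawal path is limited. This stands. Carry-over remains possible in any recent user.
- **No frequency or effect size is available.** This stands. The figures above describe weight, dose and timing, not bias.
- **The document is a condensed article, and the full protocol may hold a longer list of prohibited drugs.** This is fair for how prior medication is recorded. But the article states the exclusion itself, with its classes and window, and as stated it admits these women.
- **Nothing shows that 2 weeks is enough for benzodiazepines.** This stands. The window is proposed because the protocol already uses it for the other classes.

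No claim is made about benzodiazepine use after entry. The other-therapies clause and section 2.6 may already bar it.

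**Conclusion.** The concern holds. As written, a woman without abuse or dependency who stopped a prescribed benzodiazepine shortly before inclusion meets no exclusion criterion, although she has just left the comparator's class. The consequence is a possible difference between arms in early attack frequency, PDSS and PASS, of unknown size and direction and mainly in the first 4 weeks. Each such woman carries 2.9% of her arm (3.6% after the allowed loss), so even a few count in a trial of 70.

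This rests on reading the drug list as closed and on benzodiazepines not being counted as antidepressants, which is how the Introduction treats them. The change should be made because it is cheap. It is not a flaw that invalidates the comparison.

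**What to change.** 1. In section 2.5, item 4, add benzodiazepines to the drug list under the existing 2-week window. Women should not be taken off a needed drug in order to qualify.
2. Ask about benzodiazepine use at screening, for example as one item in the baseline questionnaire of section 2.9, which already asks about previous acupuncture.
3. For women already enrolled, take benzodiazepine use in the 2 weeks before inclusion from clinic records. Where a woman came through the media route in section 2.3 and has no such record, ask her. Report the result by arm.

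The cost is an amendment to one exclusion item, one screening question and slightly fewer eligible women; how many fewer is unknown. Recruitment runs from December 2017 to December 2021 (section 3.1), 48 months for 70 women, or 70/48 ≈ 1.5 a month. Sample size and analysis do not change. The amendment cannot reach women enrolled before it, so earlier and later entrants would come in under different rules. For the earlier ones only step 3 helps.

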### Subject withdrawal criteria

2.6

1.Violation of the inclusion criteria or fulfillment of the exclusion criteria;2.Serious adverse events occur during the treatment;3.Violation of the protocol by the investigator or the subject;4.Use other medicines or treatments without permission from the investigator;5.Loss to follow-up period;6.Inappropriate progress as judged by the investigator.

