### Blinding

2.8

Since it is unachievable to apply blind method to experimental subjects of the two groups above and the experimenters, result measurers and data statisticians will be blinded.

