### Sample size calculations

2.13

Based on preliminary experiments, it is obtained that after treatment the Kuppermann index (MI) of the intervention group dropped 15.90 ± 2.71, while the control group dropped 13.84 ± 1.87, the population standard deviation S = 2.12, δ = 2.06. Given α = 0.05 bilateral, β = 0.1, power of test 1−β = 0.9, based on formula^[15]^: n = 2 × [(tα+t2β) × s/δ] × [(tα+t2β) × s/δ], calculating with trial and error method, we used table look-up: tα, ∞ = 1.96, t2β, ∞ = 1.282, then we obtained n = 23.66 ≈ 24. According to t table: t0.05(24 × 2−2) = 2.0129, t0.2(24 × 2−2) = 1.3002, we substituted it into the former formula and obtain n = 23.25 ≈ 24, the sample size was plateaued, and the attempts stopped, which means each group requires 24 samples, and 2 groups require 48 samples in total (n = 48). With the consideration of the maximum loss rate of follow up is 20%, we concluded that the total sample size is 60. According to HAMA Score (14 items contained), the sample size is 14 × 5 = 70. Take two parts above into consideration, the sample size is determined at 70.

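### Section 2.6 allows withdrawal of randomised patients for outcome-related reasons in an open trial and does not separate stopping treatment from ending follow-up, so the week-12 and follow-up comparison is at risk of selection bias

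*Protocol article*

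**What the plan says.** Section 2.6 (Subject withdrawal criteria) is a list of six items with no stated consequence beyond its heading. Four matter most here:

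- Criterion 2: "Serious adverse events occur during the treatment". This shows that the list operates after randomisation.
- Criterion 3: "Violation of the protocol by the investigator or the subject".
- Criterion 4: "Use other medicines or treatments without permission from the investigator".
- Criterion 6: "Inappropriate progress as judged by the investigator".

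Criterion 5, in the same list, is loss to follow-up.

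Section 2.8 (Blinding) says "Since it is unachievable to apply blind method to experimental subjects of the two groups above and the experimenters", and then that "result measurers and data statisticians will be blinded".

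Section 2.10.1 schedules the primary outcomes (attack frequency, PDSS, PASS) at weeks 0, 4, 8 and 12 and during follow-up. It does not say whether withdrawn patients keep those visits. Section 2.13 allows for a maximum loss to follow-up of 20%.

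**The concern.** The heading of 2.6 withdraws the subject, not the treatment. Placing loss to follow-up beside the other five items suggests that all six are ways of leaving the study. Criterion 6 depends on progress by its own words and leaves the term undefined. Criterion 4 turns on the investigator's permission, and criterion 3 can be triggered by the investigator's own conduct.

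The arms are an embedding procedure and a daily tablet, and both patients and experimenters know which is which. Withdrawal on these grounds can therefore be related to outcome and can differ between arms. Blinding the outcome assessors does not help for a patient who is no longer assessed.

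What is at stake is the comparability that randomisation provides. Whether visits continue after withdrawal is a rule of conduct. Once visits have been missed, the analysis can only impute what they would have shown.

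**Working it through.** **Step 1. The plan's own figures: is this a matter of numbers?** Inputs from section 2.13: δ = 2.06 and S = 2.12 on the Kuppermann index; "Given α = 0.05 bilateral, β = 0.1, power of test 1−β = 0.9"; t values 2.0129 and 1.3002.

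- n per group = 2 × [(2.0129 + 1.3002) × 2.12 / 2.06]² = 23.25, so 24, as stated.
- Total with 20% loss = 48 / (1 − 0.20) = 60, as stated. The final size is 70, or 35 per arm.
- A 20% loss from 35 leaves 35 − 7 = 28 per arm. On the same inputs, noncentral-t power is 94.6% at 28 per arm, against 98.0% at 35.

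A loss of the size allowed for leaves the stated 90% power intact. What remains is the question of who is lost.

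**Step 2. Size of the selection effect if withdrawn patients are not assessed.** Assumptions, none given in the documents: 35 per arm; no true difference; outcome standard normal with higher values better; judged progress correlated ρ with the week-12 outcome; the worst-progressing patients lost and the rest compared by a two-sided 5% t test.

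Let m(k) be the expected mean of the best k out of 35 standard normal values. Then

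bias = ρ × [m(kA) − m(kB)], in SD units, in favour of the arm that loses more.

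Here m(35) = 0, m(31) = 0.2101 and m(28) = 0.3400. Losing 7 of 35 is 20%; losing 4 of 35 is 11.4%, called about 10% below.

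- 20% versus 0%: ρ × 0.3400 = 0.170, 0.238 and 0.340 at ρ = 0.5, 0.7 and 1.0.
- 20% versus about 10%: ρ × (0.3400 − 0.2101) = ρ × 0.1299 = 0.06495, 0.091 and 0.130.
- 20% in both arms: 0.

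Type I error comes from simulation, 20,000 trials per scenario:

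| Loss, one arm vs other | ρ = 0.5 | ρ = 0.7 | ρ = 1.0 |
|---|---|---|---|
| 20% vs 0% | 10.5% | 17.5% | 32.1% |
| 20% vs about 10% | 6.2% | 8.6% | 13.7% |
| 20% vs 20% | 5.8% | 7.1% | 10.2% |

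Equal loss raises the error slightly without bias, because trimming the worst patients makes the observed spread too small for the t test.

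**Step 3. The same trials with every patient kept.** When all 70 are compared as randomised, the bias is 0 and the simulated type I error is 4.5% to 5.5%.

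**The case against.** The strongest reply is that the article gives only a bare list. It never says that withdrawn patients stop assessments or leave the analysis. It condenses a full protocol that is not shown, and the choice of analysis set is commonly left to that document or to the SAP. This stands, and the absence of a named analysis set is not raised here. A reader might infer that the groups compared at week 12 are no longer the groups randomised. The documents do not support that as a fact, because it needs two steps they do not state: that outcomes cease to be collected, and that these patients are excluded.

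Four further limits also stand:

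- Only criterion 6 is expressly a matter of investigator judgement. Criterion 4 turns on permission, and criterion 3 names no judge. Section 2.8 does not say outright that the investigator of 2.6 is one of the unblinded experimenters, though nothing places that person among the blinded roles.
- Reading criterion 6 as poor progress is an interpretation of an undefined term.
- A reader might infer that embedding patients, who receive no study drug, would seek other medication more often and that the bias would favour embedding. No passage says so. The adverse reactions to alprazolam listed in section 2.12 make greater withdrawal from the medication arm just as conceivable.
- The 20% in section 2.13 is an overall allowance, neither arm-specific nor linked to outcome.

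What the reply does not remove is that 2.6 is the section governing withdrawal. As written, it permits outcome-related withdrawal and leaves open whether assessment continues.

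**Conclusion.** The point holds as a conditional risk. Section 2.6 permits withdrawal that can depend on outcome and on the open treatment, most clearly through criterion 6 and to a lesser degree through 3 and 4. It does not distinguish leaving treatment from leaving follow-up. Unless withdrawn patients are still assessed, the week-12 and follow-up comparison is exposed to selection bias of unknown direction.

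The illustrated size runs from no bias (equal loss), through 0.06 to 0.13 SD (20% versus about 10%), to 0.17 to 0.34 SD (20% versus none). The last is a deliberately unfavourable case. Loss rates, correlations and the rule that the worst-progressing patients leave are all assumptions, so the figures show what could happen and are not a forecast. The change is worth making because it is cheap and outcomes not collected cannot be recovered. Confidence is moderate, since the full protocol may already settle the matter.

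**What to change.** - State in section 2.6 that meeting criteria 1 to 4 or 6 does not end outcome collection. These patients keep their week 4, 8, 12 and follow-up assessments unless they withdraw consent. Criterion 5, loss to follow-up, is a different kind of event and should be listed separately.
- State that all randomised patients are compared in the arm to which they were assigned.
- Record the type and start date of any other treatment, so that its influence can be described.

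The clinical rules on when allocated treatment stops are left unchanged. An analysis counting withdrawn patients as non-responders is not proposed, because section 2.10 defines no responder endpoint.

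The cost is amendment wording and the effort of keeping visits that are already scheduled. The small downside is that some outcomes will be measured off the assigned treatment, which the report should say. If the full protocol already provides for continued assessment, it is enough to say so in 2.6.
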